### Outcome measurements

#### Primary outcomes

The primary outcome is the rate of ongoing pregnancy. It is defined as a detectable fetal heartbeat after 12 weeks of gestation.

#### Secondary outcomes

Secondary outcomes include the following six aspects: (1) endometrial type, (2) RI and PI of bilateral uterine artery and endometrial blood flow, (3) E_2_ and P, (4) biochemical pregnancy rate, (5) implantation rate, and (6) clinical pregnancy rate. The first three secondary outcomes will be compared with baseline in the mid-luteal phase of the third menstrual cycle. The first two secondary outcomes will be measured using transvaginal ultrasound and Doppler after the patient emptied the bladder and rested for 15 min (ultrasound with Siemens G50, probes 4/9 MHz) [29]. Biochemical pregnancy is defined as a positive pregnancy test result (serum β-hCG levels > 10 mIU/mL) 12 to15 days after FET. The implantation rate refers to the number of gestational sacs scanned by transvaginal ultrasound/ the total number of embryos transferred. Clinical pregnancy rate is defined as the presence of a gestational sac on ultrasound with fetal heart tones at 7 weeks of gestation.

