**Fig. 2 Fig2:**
[figure not shown]
The study flowchart

**Table 1 Tab1:** Schedule of the study process (SPIRIT figure)

	Study period						
	Enrollment	Post allocation					
Timepoint	1st visit	1st MC	2nd MC	3rd MC	4th MC	14 days after FET	3 months after FET

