**Assessments:**							
Serum estrogen					√	√	√
Serum progesterone					√	√	√
Ultrasonography	√	√	√	√	√	√	√
Pregnancy test					√	√	
Pregnancy outcome					√	√	√
Telephone follow-up						√	√

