**Fig. 3 Fig3:**
[figure not shown]
The operation process of the herb-partitioned moxibustion on the navel

For the artificial cycle operation, oral estradiol valerate 4–6 mg will be given once a day starting from the fourth menstrual cycle day 3 to 5 of the fourth menstrual cycle. When the thickness of the endometrium is > 7 mm on vaginal B ultrasound, patients will be administered with dydrogesterone (10 mg three times per day, orally) and progestin (40 mg daily, intramuscularly). FET will then be performed 3 days after administration of dydrogesterone and progestin. Progesterone will be administered after FET for sustained luteal support until 10 weeks after gestation. But when the endometrial thickness exceeds 15 mm, the FET will be canceled.

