#### Data analysis

Data will be analyzed using SPSS software version 26.0 (IBM Corp, Armonk, NY). An intention-to-treat analysis (ITT) will be performed to explore the effectiveness of the trial. Patients in the treatment group will be included in the ITT analysis even if they had not completed the herb-partitioned moxibustion on the navel. Continuous variables that will meet the requirements for normal distribution will be represented as mean ± SD. Continuous variables that will not follow normal distribution will be represented as median and IQR. Categorical variables will be reported as absolute and relative percentage frequency. Independent Student *T*-test or Mann-Whitney *U* test will be used to explore differences in mean or median between the treatment group and the control group for continuous variables. Pearson *χ*^2^ test will then be performed to compare baseline characteristics and results for categorical variables. Paired sample *T*-test will be used to compare before and after treatment within-group differences. Multiple imputation will be used to process missing values in the data of this study. All tests will be two-tailed, and the significance level will be set as *P* < 0.05.

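### The stated E2 and P comparison needs a baseline and a third-cycle value, but Table 1 schedules hormone samples at neither time

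*Protocol article*

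**What the plan says.** In the Protocol article, Secondary outcomes lists six items, and the hormones are the third: "3) E_2_ and P, (4) biochemical pregnancy rate". The timing of items one to three is then fixed in one sentence: "The first three secondary outcomes will be compared with baseline in the mid-luteal phase of the third menstrual cycle".

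Table 1, the SPIRIT schedule, has seven time columns: first visit, menstrual cycles one to four, 14 days after transfer and 3 months after transfer. The rows "Serum estrogen" and "Serum progesterone" are ticked in the last three columns only. The row "Ultrasonography", which serves items one and two, is ticked in all seven.

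The Treatment group and Control group sections place moxibustion (treatment arm only) in cycles one to three and the artificial cycle (both arms) in cycle four. In the artificial cycle, "oral estradiol valerate 4–6 mg will be given once a day", and progestogens follow. Data analysis plans between-group tests, multiple imputation for missing values, and a paired t-test that "will be used to compare before and after treatment within-group differences".

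**The concern.** The outcome definition and the assessment schedule are both stated in the article, and they disagree about when the hormones are measured. This is not detail left to a fuller document. An analysis plan could not repair it either, because no analysis can use blood that was not drawn.

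A schedule table is what staff usually work from when they book visits and build the case report form. If Table 1 is used in that way, a secondary outcome that is also named in the abstract will have neither its before value nor its after value. Those samples cannot be taken later: once a woman has begun moxibustion her pre-treatment value is gone, and once the third cycle has passed so is that value. Trial status gives 15 July 2021 for the first recruitment and 31 December 2021 as the expected end of recruitment, so the chance of correction shrinks with each woman treated.

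**Working it through.** The plan states no figure on this point, so there is none to reproduce. The check sets the times that the outcome needs against the times that the schedule provides.

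**Inputs.** Required times come from Secondary outcomes. Scheduled times come from Table 1. The timing of treatment comes from Treatment group and Control group.

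| Time column in Table 1 | Needed for the E2/P outcome | Hormone sample ticked | Ultrasound ticked |
|---|---|---|---|
| First visit (the only column before cycle one) | yes, as baseline | no | yes |
| Cycle 1 | no | no | yes |
| Cycle 2 | no | no | yes |
| Cycle 3 | yes, mid-luteal | no | yes |
| Cycle 4 | no | yes | yes |
| 14 days after transfer | no | yes | yes |
| 3 months after transfer | no | yes | yes |

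**Step 1, overlap.** Hormones: required times with a tick = 0 of 2. Ultrasound: 2 of 2. If baseline were instead read as a sample early in cycle one, before the first session, the hormone count would still be 0 of 2, because cycle one has no hormone tick.

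**Step 2, is the table misread?** Each row splits into exactly seven cells. With the same alignment, moxibustion falls in cycles 1 to 3, the artificial cycle in cycle 4, and telephone follow-up in the two post-transfer columns, all of which makes sense against the text. A shifted column is therefore unlikely.

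**Step 3, can the scheduled samples stand in?** Moxibustion ends with cycle 3. All three hormone ticks lie in cycle 4 or later, so none is a pre-treatment value and none is a third-cycle value. Cycle 4 is also a hormonally prepared cycle in both arms.

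**Step 4, what happens to the analysis?**
- The paired test uses d = (third-cycle value) − (baseline value) for each woman. With neither term scheduled, d is undefined for all 105 + 105 = 210 planned women.
- A between-group test at the third-cycle visit needs only the second term, but that is not scheduled either.
- Multiple imputation estimates missing values from their relation to other variables among women in whom they were observed. For a variable observed in nobody, that relation cannot be estimated.

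**The case against.** The strongest reply is that the text itself prescribes the measurement, so the slip may lie only in the table and staff may be drawing the samples as the text says. That stands: the article does not settle which statement is intended, and the loss of data depends on Table 1 being followed. It does not remove the contradiction. It also stands that this is one of six secondary outcomes and that nothing in the primary outcome or the sample size depends on it.

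A reader might go further in two ways that the document does not support.

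- One might infer that every scheduled hormone sample is taken under hormone support or in pregnancy. Table 1 gives no day for the cycle-4 sample, and estradiol starts on day 3 to 5, so the sample could come before the first dose. At 3 months after transfer, a woman who did not conceive is not pregnant and is past the stated 10-week limit of luteal support. The argument needs only the weaker fact that all three samples come after the third cycle.
- One might infer that the ultrasound outcomes have the same fault, with a baseline scan taken at an arbitrary cycle phase. Ultrasound is ticked at both required times. The article is silent on the cycle day of the baseline scan, and a condensed article may leave visit windows to the full protocol. Any mismatch in phase would also apply to both randomised arms alike, leaving the between-group comparison at the third-cycle visit valid.

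**Conclusion.** The point holds for E2 and P only. The outcome definition requires two hormone values, Table 1 schedules neither, and nothing else in the article schedules them. Followed as printed, Table 1 leaves the stated comparison and its paired test without data for all 210 women. If staff follow the text instead, the samples exist and the error is confined to the table. It would be wrong to conclude that the data are certain to be lost.

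The conclusion rests on two assumptions: that the columns of Table 1 were read correctly, which the other rows support, and that baseline means a time before the first moxibustion session. This should be fixed, but it does not threaten the trial's main conclusion.

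**What to change.** Decide which statement is intended and make Secondary outcomes and Table 1 agree.

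- **If the text is intended:** tick serum E2 and P at baseline, before the first moxibustion session, and at the third-cycle mid-luteal visit, in both arms, in Table 1 and on the case report form. Women already treated without a baseline sample should enter the between-group third-cycle comparison only. Report how many there are in each arm, and do not impute a baseline for them as if it had been planned and missed at random.
- **If Table 1 is intended:** redefine the third outcome as a between-group comparison of E2 and P at the scheduled times, and drop the comparison with baseline and the paired test for these two hormones. The outcome would then describe hormone levels in and after the artificial cycle, which is a different question, and the text should say so.

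The second option is an edit to the text. The first is an amendment to Table 1 and the case report form, plus two samples per woman that the outcome definition already calls for. The paperwork is small in either case, but under the first option pre-treatment values for women already treated cannot be recovered if they were not drawn. A change of study procedure needs a formal amendment under the article's Protocol amendments section.

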## Abstract

**Background:**

Recurrent implantation failure (RIF) in the majority of patients undergoing in vitro fertilization and embryo transfer (IVF-ET) is caused by various factors such as maternal age, embryo quality, endometrial receptivity (ER), and immunity. The incidence of RIF is usually between 5 and 10%. Previous studies have shown that herb-partitioned moxibustion on the navel is one of the treatment methods of acupuncture with a positive effect on pregnancy. However, its application in the treatment of RIF has not been reported. Therefore, this study aims to evaluate the effectiveness and safeness of herb-partitioned moxibustion on the navel in improving the outcome of frozen embryo transfer (FET) in patients with RIF.

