### Eligibility criteria

#### Inclusion criteria

Patients who meet the following criteria will be enrolled in this study:

(1) Patients with RIF (comprising patients who fail to achieve a clinical pregnancy after transplantation of ≥ 4 high-quality embryos in ≥ 3 fresh or frozen cycles [11]) and (2) patients who have undergone in vitro fertilization through GnRH-antagonist protocol with the number of high-quality embryos ≥ 2.

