### Statistical analysis

#### Sample size calculation

The PASS software version 11.0 (NCSS, LLC. Kaysville, Utah, USA.) was used to estimate the sample size. According to a previous study [30], when the sample size of the treatment group and control group is 94 and 94 respectively, 80% of the power was achieved to detect the assumed rate of ongoing pregnancy in the untreated control group versus the effect size to be examined for (20%). The test statistic used was the two-sided *Z* test with pooled variance and the significance level of the test is 0.05. The significance level achieved in this design was 0.0496. The lost follow-up rate will be estimated by 10% and the final sample size of the treatment group and control group was 105 cases each and the total sample size was 210 cases.

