#### Randomization and allocation

Participants will be randomly allocated into treatment or control groups at a rate of 1:1 by a computer-generated randomization sequence generated by the data coordinating center with SAS software version 9.2 (SAS Institute, Cary, NC). Allocation will be made by a designated researcher who will have no contact with any participant and will not be involved in the collection and analysis of the data. Due to the nature of the intervention, it will not be feasible to conceal the allocation from the practitioner and participants. The practitioner will not be allowed to disclose any information concerning their treatment to the participants or the assessor.

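### Implantation rate is counted per embryo, but the only between-group test given for categorical results is a Pearson chi-square; if more than one embryo is transferred, that test ignores within-woman correlation.

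*Protocol article*

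**What the plan says.** Three statements in the protocol article have to be read together.

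- **Outcome (Secondary outcomes).** Implantation rate is "the number of gestational sacs scanned by transvaginal ultrasound/ the total number of embryos transferred". The denominator is all embryos, pooled over women.
- **Randomisation (Randomization and allocation).** "Participants will be randomly allocated into treatment or control groups at a rate of 1:1". The randomised unit is the woman.
- **Test (Data analysis).** A Pearson chi-square "test will then be performed to compare baseline characteristics and results for categorical variables". For continuous variables the section gives a t-test or Mann-Whitney test. "All tests will be two-tailed, and the significance level will be set as" P < 0.05. No method is named for several embryos from one woman, and the implantation rate is not mentioned in this section.

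Eligibility requires women "with the number of high-quality embryos ≥ 2". That concerns embryos obtained. The number transferred per frozen cycle is neither stated nor limited to one.

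**The concern.** A Pearson chi-square on a table of embryos by arm treats every embryo as a separate observation. Embryos placed in the same uterus are unlikely to be independent. The abstract itself describes implantation failure as "caused by various factors such as maternal age, embryo quality, endometrial receptivity (ER), and immunity"; age, receptivity and immunity are shared by all embryos of one woman, and receptivity is what the treatment is meant to improve. A positive correlation therefore follows from the trial's own rationale.

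With positive correlation, the variance of the difference in implantation rates is larger than the chi-square assumes, so the P value is too small. Implantation is one of three pregnancy-related secondary outcomes and lies close to the condition being treated, so a spuriously small P value could readily be cited as support.

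**Working it through.** **The plan's own figures.** The protocol states no figure for the implantation test beyond the nominal two-sided 0.05. Its sample size concerns the primary outcome: "when the sample size of the treatment group and control group is 94 and 94 respectively", "80% of the power was achieved", with an achieved significance level of 0.0496. No control rate is given. Taking 30% against 50% (a back-solved assumption, reading the 20% effect as percentage points), the pooled normal formula gives 93 per arm. Exact enumeration at 94 per arm gives power 0.8002 and alpha 0.0496, which matches. Allowing for 10% loss, 94 / 0.90 = 104.4, rounded up to 105 per arm and 210 in total. The calculation counts women, so embryo clustering does not enter it.

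**Inputs for the implantation test**

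- From the protocol: nominal two-sided alpha 0.05; 94 evaluable or 105 randomised women per arm.
- Assumed: embryos per transfer (m), with all women receiving one, half receiving two and the rest one, or all receiving two.
- Assumed: within-woman correlation (ICC) of 0 to 0.5.

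**Formulas**

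- Equal m: DE = 1 + (m − 1) × ICC.
- Mixed m: DE = 1 + (Σm²/Σm − 1) × ICC.
- True type I error of the unadjusted test: 2 × [1 − Φ(1.96/√DE)].

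If half the women receive two embryos, Σm²/Σm = (0.5 × 4 + 0.5 × 1) / (0.5 × 2 + 0.5 × 1) = 2.5/1.5 = 1.667, so DE = 1 + 0.667 × ICC. If all receive two, DE = 1 + ICC.

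| ICC | One embryo each | Half with two: DE, error | All with two: DE, error |
|---|---|---|---|
| 0 | 5.0% | 1.000, 5.0% | 1.0, 5.0% |
| 0.1 | 5.0% | 1.067, 5.8% | 1.1, 6.2% |
| 0.3 | 5.0% | 1.200, 7.4% | 1.3, 8.6% |
| 0.5 | 5.0% | 1.333, 9.0% | 1.5, 11.0% |

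For example, with all women receiving two embryos and ICC 0.3, 1.96/√1.3 = 1.719 and the two-sided tail is 0.086.

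**Check by simulation.** With 100,000 trials per setting, 94 or 105 women per arm and implantation probabilities of 0.2 to 0.4, the rejection rates were:

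- half with two embryos: 5.6% to 5.9% at ICC 0.1 and 8.9% to 9.2% at ICC 0.5;
- all with two embryos: 6.1% to 6.4% at ICC 0.1 and 10.9% to 11.3% at ICC 0.5;
- one embryo each: 4.8% to 5.2% at every ICC.

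**Width of a corrected interval.** The standard error grows by √DE: √1.1 = 1.05 and √1.5 = 1.22, that is, about 5% to 22%.

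**The case against.** The strongest reply is that the protocol nowhere says the implantation rate will be tested by chi-square. The Data analysis section gives a generic list of tests, and a per-woman proportion of sacs to embryos could be compared with the t-test or Mann-Whitney test in that list. The handling of several embryos per woman might also be left to a statistical analysis plan that is not shown. It is true that the chi-square reaches this outcome only through the general rule. But the definition divides by the total number of embryos, which points to a pooled rate and not to one proportion per woman, and the only between-group test for categorical results is unsuited to that pooled rate. The point is therefore about what the text fixes, not about missing detail.

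A second reply is that the inflation may not exist, and this stands as a condition. The minimum of two high-quality embryos does not fix how many are transferred. Multiple transfer is plausible: a woman who just meets the eligibility definition, with four embryos over three cycles, must have had at least one past transfer of more than one embryo. It is still not documented for this trial. A reader might infer that the false-positive rate is certainly inflated; the documents support only the conditional statement.

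A reader might also object that women with more embryos carry more weight. That is a property of the outcome as defined, not an error of the test, and a GEE on embryos does not remove it.

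**Conclusion.** The mismatch is real but conditional and confined to one secondary outcome. If the general chi-square rule is applied to embryos and some women receive more than one, the type I error exceeds 5%. The range is about 5.8% to 9.0% with half the women receiving two embryos and 6.2% to 11.0% with all receiving two, for ICC 0.1 to 0.5. Embryos per transfer and ICC are both assumptions; if either all transfers are single or the ICC is 0, there is nothing to correct.

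It would be wrong to infer that the trial's main conclusion is at risk. Ongoing pregnancy, biochemical pregnancy and clinical pregnancy are events per woman, the sample size is unaffected, and the protocol ties no decision to the implantation rate.

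**What to change.** In the Data analysis section, state that the implantation rate will be compared between arms with the woman as the cluster, in place of an embryo-level chi-square. A logistic GEE on sacs out of embryos with robust standard errors does this and is available in SPSS 26; an independence working correlation keeps the pooled per-embryo rate as the quantity compared. Report the number of embryos transferred by arm.

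If equal weight per woman is wanted, compare per-woman proportions instead and redefine the outcome accordingly in the Secondary outcomes section. The two options can answer different questions, so one should be chosen in advance.

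The cost is a change of wording, with no new data and no change in sample size. The confidence interval widens by about 5% to 22% at variance inflation of 1.1 to 1.5. If every woman receives a single embryo, the correction costs essentially nothing.

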#### Retention

The research assistant will conduct weekly follow-ups to remind the participants of upcoming doctor/data collection appointments after enrollment and will record any adverse effects of the herb-partitioned moxibustion on the navel.

### Statistical analysis

#### Sample size calculation

The PASS software version 11.0 (NCSS, LLC. Kaysville, Utah, USA.) was used to estimate the sample size. According to a previous study [30], when the sample size of the treatment group and control group is 94 and 94 respectively, 80% of the power was achieved to detect the assumed rate of ongoing pregnancy in the untreated control group versus the effect size to be examined for (20%). The test statistic used was the two-sided *Z* test with pooled variance and the significance level of the test is 0.05. The significance level achieved in this design was 0.0496. The lost follow-up rate will be estimated by 10% and the final sample size of the treatment group and control group was 105 cases each and the total sample size was 210 cases.

#### Randomization and allocation

Participants will be randomly allocated into treatment or control groups at a rate of 1:1 by a computer-generated randomization sequence generated by the data coordinating center with SAS software version 9.2 (SAS Institute, Cary, NC). Allocation will be made by a designated researcher who will have no contact with any participant and will not be involved in the collection and analysis of the data. Due to the nature of the intervention, it will not be feasible to conceal the allocation from the practitioner and participants. The practitioner will not be allowed to disclose any information concerning their treatment to the participants or the assessor.

#### Data management and monitoring

Three levels of data monitoring will be used to improve quality control. The reproductive medicine practitioner will make the trial and study plan available to all participant, and those who met the inclusion criteria and expressed interest in participating will sign the written informed consent form. The participant’s demographic information will be carefully recorded on the CRF. The supervisors will check the CRF for completeness and accuracy of input data. Any errors will be underlined, corrected, and signed by the corresponding investigator. An independent data monitoring committee (DMC) consisting of an epidemiologist, an acupuncture specialist, and a gynecologist will monitor and evaluate the recruitment of subjects, the progress of research implementation, and safety, confidentiality, and integrity of obtained data monthly. In addition, the DMC will regularly submit audit reports to the project management department. Further, it will provide recommendations for continuing the clinical trial, modifying the trial protocol, or terminating the trial.

